## Abstract

**Background:**

Non-alcoholic fatty liver disease (NAFLD) is a liver manifestation of metabolic syndrome since obesity and insulin resistance are the main pathogenic contributors for both conditions. NAFLD carries increased risk of atherosclerosis and cardiovascular diseases. There is an urgent need to find effective and safe therapy for children and adults with NAFLD. Data from research and clinical studies suggest that omega-3 fatty acids may be beneficial in metabolic syndrome-related conditions and can reduce the risk of cardiovascular disease.

**Methods/design:**

We are conducting a randomized, multicenter, double-blind, placebo-controlled trial of treatment with omega-3 fatty acids in children with NAFLD. Patients are randomized to receive either omega-3 fatty acids containing docosahexaenoic acid (DHA) and eicosapentaenoic acid (EPA) or placebo for 24 weeks. The dose of omega-3 (DHA+ EPA) ranges from 450 to 1300 mg daily. Low calorie diet and increased physical activity are advised and monitored using validated questionnaires. The primary outcome of the trial is the number of patients who decreased ALT activity by ≥ 0,3 of upper limit of normal. The main secondary outcomes are improvement in the laboratory liver tests, liver steatosis on ultrasound, markers of insulin resistance and difference in fat/lean body mass composition after 6 months of intervention.

**Discussion:**

Potential efficacy of omega-3 fatty acids in the treatment of NAFLD will provide needed rationale for use of this safe diet supplement together with weight reduction therapy in the growing population of children with NAFLD.

**Trial registration:**

NCT01547910

## Background

Non-alcoholic fatty liver disease (NAFLD) comprises spectrum of liver damage that ranges from simple steatosis through steatohepatitis (NASH), fibrosis to cirrhosis, end-stage liver disease and occasionally hepatocellular carcinoma. Although the natural history of NAFLD remains yet to be defined, it is now clear that NAFLD and especially NASH carries increased risk of atherosclerosis, cardiovascular disease (CVD) and overall mortality when compared to general population [1-8]. Emerging evidence suggests that the main cause of death in NAFLD is CVD what strongly reflects its very close relation to metabolic syndrome (MS) [1-3]. In patients who develop liver steatosis at younger age the complications of the liver disease and metabolic syndrome may appear sooner, therefore they require special concern and early management.

Weight reduction appears to be the front-line therapy in NAFLD. Dietary restrictions are as important as physical activity and changes in lifestyle [9-12]. However compliance is poor in these patients and there is too much inconsistent data from the clinical trials to indicate the optimal rate and extent of weight loss in children.

Pharmacological treatment remains unsuccessful in both children and adults with NAFLD. In the planning phase of this trial we performed a systematic review of literature on pharmacological interventions for NAFLD [13]. Use of probucol, pioglitazone, metformin and carnitine in high doses may be promising but in conclusion none of the pharmacological agents could be recommended for treatment of NAFLD, especially in children. Recent two large clinical trials using vitamin E and pioglitazone in NAFLD showed conflicting results [14,15].

Omega-3 long-chain polyunsaturated fatty acids are safe diet supplements that showed efficacy in the prevention and therapy of cardiovascular diseases, dyslipidemia and metabolic syndrome [16-19]. In a paucity of effective treatment they may constitute safe pharmacological option for children with NAFLD.

Recently Parker et al. published systematic review and meta-analysis of studies of omega-3 LC-PUFA (long-chain polyunsaturated fatty acids) supplementation in adults with NAFLD [20]. Nine studies (5 RCTs), involving 355 individuals were included. Patients were given either omega-3 LC-PUFA or control treatment. Duration of therapy ranged from 8 weeks to 12 months, as well as the dose of LC-PUFA - from 0,25g to 13,7g per day. In conclusion of the review, omega-3 fatty acids were claimed beneficial vs. placebo in reducing liver fat (estimated by liver biopsy, ultrasound or 1H-MRS) (effect size = ˙0.97, 95% CI: ˙0.58 to ˙1.35, p <0.001) and decreasing AST (effect size = ˙0.97, 95% CI: ˙0.13 to ˙1.82, p = 0.02) but not ALT activity. However the current data are not sufficient to set the optimal dose of LC-PUFA in NAFLD.

So far there has been only one randomized controlled trial that assessed efficacy of LC-PUFA in children with NAFLD [21]. Patients were assigned to receive 250 mg or 500 mg of DHA (docosahexaenoic acid) per day or placebo for 6 months. Beneficial results of DHA were expressed in the improvement of level triglycerides, markers of insulin resistance and liver fat assessed by ultrasound. DHA did not show significant effect on ALT activity.

Below we describe design of our multicenter, randomized, double-blind, placebo-controlled trial of omega-3 LC-PUFA supplementation in children with NAFLD.

## Methods

### Study design overview

We are conducting a multi-center, randomized, placebo-controlled, double-blind clinical trial to assess efficacy of treatment with omega-3 LC-PUFA in children with established NAFLD. Eligible patients are randomized to two arms: these who receive either fish oil containing omega-3 LC-PUFA: docosahexaenoic acid (DHA) and eicosapentaenoic acid (EPA) (450 to 1300 mg daily), or placebo (sunflower oil) for 24 weeks.

The main aim of the study is to determine whether supplementation of omega-3 LC-PUFA improves biochemical parameters of liver function, markers of insulin resistance, serum lipid profile and liver steatosis on ultrasound in patients with non-alcoholic fatty liver disease. Primary comparisons will be made using an intention-to-treat analysis at week 12 and 24. Per protocol analysis will be also applied for the same time points. The follow-up visit is planned after 6 months after discontinuation of study treatment. A schematic of the trial design is shown on Figure 1.

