### Outcome measures

Primary outcome measure of the study is a number of patients in whom ALT level decreased by minimum 0,3 ULN (upper limit of normal) after the 6 months of treatment with omega-3 when compared to the placebo group.

Secondary outcomes include the following parameters compared between omega-3 and placebo group after 6 months of treatment:

▪ normalization of ALT activity at week 24

▪ decrease of ALT, AST, GGTP and other liver function tests,

▪ normalization or improvement of liver steatosis on ultrasound based on Saverymuttu scoring system [29],

▪ changes in the level of fasting glucose and insulin, cholesterol and lipid profile,

▪ changes in insulin resistance markers as insulin, HOMA-IR, adipokines,

▪ alterations in the basic hematology and biochemical lab tests,

▪ difference in fat and lean body mass measurements (using electric bioimpedance TANITA® Body Composition Analyzer BC 418MA),

▪ caloric intake as well as intake of fats, fatty acids and sucrose.

Other outcomes comprise of changes in anthropometric measures of body weight (e.g. height, hip/waist circumference, triceps, subscapular and abdominal skinfolds thickness) as well as vital signs like heart rate and blood pressure.

In selected subgroups of patients we will also examine effect of treatment on:

▪ serum antioxidants e.g. glutathione, glutathione peroxidase, tromboxane,

▪ cytokines e.g. TNF-α

▪ fatty acid composition of plasma phospholipids [%wt/wt],

▪ bone mass density and fat content using dual x-ray absorptiometry (DEXA) (Lunar Prodigy, General Electric Healthcare, United States) - in a subgroup of patients who were eligible for this investigation in 2 centers,

▪ liver imaging by MR and fat content on 1H-MRS - in subgroups of patients who were eligible for these investigations,

▪ adipose tissue distribution on MRI - in a subgroup of patients who were eligible for this investigation in 1 center.

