### Sample size

We decided to use decrease of ALT by 0.3 upper limit of normal value as the primary endpoint of the study. It was estimated that a sample size of 80 patients would be sufficient to reveal a difference in the treatment effect of 30% (45% in experimental group vs. 15% in control group) considering α = 0.05 and a power (β) of 80%. The number of 80 children accounted for approximately 20% withdrawals or losses. The sample size was calculated with StatDirect software version 2.7.9 (StatsDirect Ltd., England, UK).

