### Statistical analysis

Data will be presented as medians with quartile range. The Mann–Whitney U test will be used for comparisons of median values between groups. The calculations will be performed with PASW Statistics 18 version 18.0.0, Polar Engineering and Consulting®.

For the categorical data analysis (for the primary end point and selected secondary end points) data will be organized in contingency tables, tested for difference between observed and expected values and appropriate tests will be applied to test the null hypothesis of no difference between the groups (chi-square or Fischer’s exact test) with StatsDirect version 2.7.9 (StatsDirect Ltd., England, UK). The differences will be regarded significant at p<0.05. Statistical methods will be applied for intention-to-treat and per protocol analysis.

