**Laboratory tests:**				
- hematology	X		X	
- ALT,AST, GGTP, bilirubin, INR	X	X	X	X
- fasting glucose, insulin	X	X	X	X
- OGTT glucose, insulin 0-240mins	X			
- fasting lipids profile	X		X	X
- adipokines, cytokines, antioxidants	X		X	
- fatty acid composition of plasma phospholipids	X		X	
^**a**^**DEXA**	X		X	
^**a**^**MRI - body fat distribution**	X		X	
^**a**^**1H-MRS - liver fat content**	X		X	

^a^Done in selected patients.

Vital signs: mean BP, HR and temperature.

Anthropometry includes measurements of body weight and height, waist, hips and mid upper arm circumference (IOTF, WHO), triceps, abdominal and subscapular skin fold thickness.

OGTT glucose and insulin measurements were performed in intervals every 30 minutes from 0 to 240 minutes.

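### The design overview places the primary comparisons at weeks 12 and 24, but the primary outcome is defined at 6 months only, which leaves open two unadjusted chances of a positive primary result

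*Protocol article*

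**What the plan says.** All places are in the protocol article.

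- **Study design overview:** "Primary comparisons will be made using an intention-to-treat analysis at week 12 and 24". The next sentence adds: "Per protocol analysis will be also applied for the same time points".
- **Outcome measures:** one primary outcome, the number of children whose ALT fell by at least 0.3 ULN, assessed "after the 6 months of treatment with omega-3 when compared to the placebo group". The secondary outcomes are also placed after 6 months.
- **Sample size:** 80 children for 45% against 15% responders, "considering α = 0.05 and a power (β) of 80"%, with about 20% losses allowed for. This is a single contrast.
- **Statistical analysis:** chi-square or Fisher's exact test for the primary endpoint, and "The differences will be regarded significant at p<0.05". No split of alpha, testing order or both-must-succeed rule is given.
- **Table 2, Laboratory tests:** the row "ALT,AST, GGTP, bilirubin, INR X X X X" shows ALT at M0, M1 (week 12), M2 (week 24) and M3.

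**The concern.** The overview attaches the word primary to two time points and the endpoint definition attaches it to one. Because ALT is drawn at M1, the same responder test can be run at week 12, so the choice between the two statements is a practical one. An analyst who follows the overview could report a week-12 difference as a positive primary result even if it has gone by week 24. An analyst who follows the endpoint definition could not.

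What is at stake is the type I error of the trial's main conclusion. The Discussion says that a positive result will establish omega-3 as a useful agent in children with NAFLD, so the text should say which single test delivers that result.

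**Working it through.** **Inputs from the article.** Two-sided 0.05 per test (sidedness is not stated; two-sided is assumed). Design rates 45% and 15%. N = 80 planned with about 20% losses. 38 per arm randomised. Chi-square or Fisher's exact test.

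**Inputs assumed.** The correlation between weeks 12 and 24 is not given, so a range is shown. Under the null, a common responder rate of 15% (the design control rate) or 30% (the midpoint of 15% and 45%) is used, the same at both visits. All 38 per arm are counted at both visits.

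**Step 1. The stated sample size is for one comparison.** Unpooled formula per arm:

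n = (1.96 + 0.842)² × (0.45×0.55 + 0.15×0.85) / 0.30² = 7.85 × 0.375 / 0.09 = 32.7, so 33.

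33 × 1.2 = 39.6, so 40 per arm, or 80 in total. (Dividing by 0.8 instead gives 82.) The stated 80 is reproduced with the full 0.05 spent on one test.

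**Step 2. Either week suffices, normal approximation.**

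Independent tests: 1 − (1 − 0.05)² = 0.0975.

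Correlated tests: 1 − P(|Z₁| < 1.96 and |Z₂| < 1.96), bivariate normal with correlation r.

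| r | Either week, two-sided | Either week, favouring omega-3 |
|---|---|---|
| 0 | 9.75% | 4.9% |
| 0.5 | 9.1% | 4.5% |
| 0.7 | 8.4% | 4.2% |
| 0.8 | 7.8% | 3.9% |
| 0.9 | 7.0% | 3.5% |

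The single-test references are 5% and 2.5%.

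**Step 3. Either week suffices, with the tests the plan names.** Responder status at each visit comes from a bivariate normal latent variable cut at the responder rate, 38 per arm. The single-visit rate is exact. The either-week rate comes from 400,000 simulated trials at each latent correlation.

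| Test | Responder rate | Week 24 alone | Either week, latent correlation 0 to 0.9 |
|---|---|---|---|
| Chi-square, uncorrected | 15% | 5.3% | 10.4% to 9.0% |
| Chi-square, uncorrected | 30% | 5.2% | 10.0% to 8.5% |
| Fisher's exact | 15% | 2.4% | 4.8% to 4.2% |
| Fisher's exact | 30% | 3.0% | 5.9% to 5.0% |

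Fisher's test is conservative at this size, so testing twice takes it only to around 5%. It still multiplies its own single-visit rate by about 1.7 to 2 (for example 4.2/2.4 and 4.8/2.4).

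**Step 4. The other readings.** If the Outcome measures section governs, there is one test and the rate is that of one test. If both weeks had to succeed, the rate could not exceed the single-test rate.

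**Step 5. Cost of keeping both weeks primary.** At 0.025 each, the Step 1 formula gives 39.6, so 40 evaluable per arm (80), or 80/0.8 = 100 with 20% losses. The trial randomised 76.

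**The case against.** The strongest reply is that the overview sentence is not about time points at all. It is followed at once by the per-protocol sentence, so primary may be meant only to rank intention-to-treat above per-protocol, with the two on-treatment visits listed in passing. The Outcome measures section is where endpoints are defined, it names one outcome at one time, and the sample size agrees with it. A condensed article may also leave the testing order to a fuller plan that is not shown.

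Much of this stands. It may well be what was meant, and the absence of an alpha split is not in itself the finding. What remains is that two statements in the same article disagree and nothing in it says which prevails.

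Three stronger readings are tempting, and the article does not support them:

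- **That the trial has an inflated error rate, well above 5%.** This needs the overview to override the endpoint definition and success at either week to suffice; the article states neither. Under Fisher's test the two-sided rate stays at about 4–6% even then.
- **That the per-protocol tests add further chances.** Counting them would give about 13% with uncorrected chi-square and an assumed 30 per arm. The overview calls only the intention-to-treat comparisons primary, so these tests do not belong in the count.
- **That lipids and ultrasound, which Table 2 does not schedule at week 12, add to the problem.** They are secondary outcomes at 6 months, and their schedule agrees with that.

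**Conclusion.** The inconsistency is real and concerns the primary comparison. As written, the article leaves open two unadjusted chances of a positive primary result; it does not establish that both will be used.

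If the overview governs and either week suffices, the two-sided false-positive rate is about 7–10% with uncorrected chi-square or the normal approximation, and about 4–6% with Fisher's exact test at 38 per arm, against 2.4–3.0% for one Fisher test. If the Outcome measures section governs, there is no inflation. The figures rest on assumed correlations of 0 to 0.9, assumed null responder rates of 15% and 30%, and complete data at both visits. Repeated ALT values in the same child are likely to be positively correlated, so the zero-correlation figures are upper ends.

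**What to change.** Change the overview sentence to agree with the Outcome measures section, for example:

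*The single primary comparison is the intention-to-treat comparison of the ALT responder proportion at week 24 (M2). Week-12 comparisons are secondary and limited to variables measured at M1. Per-protocol analyses are supportive.*

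This costs wording only: no data, visit or endpoint changes, and N = 80 stands. The Results section reports that week-24 data collection was being finalised and the full analysis was still to come, so the change should be dated and made before any unblinded comparison is seen. If the sponsor does want both weeks to be primary, the plan must state a multiplicity rule and recompute the sample size; the 0.025 split in Step 5 of the working shows the likely cost.

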**Figure 1 F1:**
[figure not shown]
Schematic of the trial design.

### Participant selection

Children aged 6 to 19 years old were recruited at the 4 Polish pediatric hospitals from July 2008 till April 2011 (the participating centers are listed in the acknowledgments). In total 76 patients were enrolled into the trial according to the screening procedures. All participants and their parents gave written consent before enrollment. Ethical approval was obtained from the Children’s Memorial Health Institute Bioethical Committee, Warsaw, Poland. The CONSORT flowchart is presented on Figure 2.

**Figure 2 F2:**
[figure not shown]
Patient CONSORT flowchart.

### Inclusion criteria

Patients had to fulfill all of the following inclusion criteria:

written consent of a patient (if at least 16 years old) and parents,

age: over 5 and below 19 years old,

overweight or obesity (BMI> 90pc according to IOTF BMI charts),

ALT activity ≥ 1,3 ULN (upper limit of normal),

hyperechogenicity of the liver on ultrasound or liver histology consistent with NAFLD/NASH (≥ 5% of hepatocytes with macrovesicular fat)

Hyper-ALT and liver steatosis on ultrasound are the most common diagnostic criteria for NAFLD used in the clinical practice. However usually the grade of ALT elevation is not defined. To increase sensitivity and specificity of diagnosis of NAFLD we used combined criteria of 1,3 ULN of ALT and liver steatosis on ultrasound. Similar diagnostic criteria were previously applied in pediatric trials on NAFLD [22,23].

### Exclusion criteria

To be eligible to participate in the trial patients had to undergo thorough screening of any other conditions that might mimic the diagnosis of NAFLD or could interfere with analysis of treatment efficacy. Exclusion criteria comprised of any pathologic conditions affecting liver as HBV, HCV infection, chronic and acute liver failure, cholestasis, metabolic diseases like α1-antitripsin deficiency, Wilson disease, diabetes mellitus, hypothyroidism, alcohol consumption etc.

Exclusion criteria:

General criteria:

•Age < 5 or > 19 years

•Current or history of significant alcohol consumption

•Unlikely to co-operate in the study, to comply with study treatment or with the study visits.

Medical and therapeutic criteria:

1. Concerning liver diseases:

•Past or active HBV infection

•Past or active HCV infection

•Chronic or acute liver failure

•Cholestasis

•Wilson disease

•Cystic fibrosis

•α1-antitripsin deficiency

•Autoimmune hepatitis

•Tyrosinemia

•Galactosemia

•Beta-oxidation disorders

•Any recognized liver disease presenting with elevated ALT other than NAFLD/NASH

2. Concerning other concomitant diseases or associated clinical conditions:

•History of diabetes mellitus

•Familiar hypercholesterolemia

•Hypothyroidism

•Current or history of craniopharyngioma

•Any medical condition that considered by physician can unable completion of the trial

3. Concerning concomitant medications:

•Treatment with vitamin E, statins, UDCA, probiotics or metformin within 3 months prior to randomization

•Pharmacological treatment of hypertension within 3 months prior to randomization

•History of parenteral nutrition

In accordance to the recent recommendations of the European Society of Pediatric Gastroenterology, Hepatology and Nutrition (ESPGHAN) on NAFLD diagnostics [24], liver biopsy was proposed to the patients in whom elevation of ALT lasted for over 6 months during weight reduction therapy.

### Treatment groups

Patients who were selected to participate in the study and gave their written consent were randomly assigned to one of the two therapeutic groups:

▪ Omega-3 group: 450-1300 mg omega-3 fatty acids (containing DHA and EPA in 3:2 proportion) in two doses per day, to be taken with morning and evening meal. The dose of omega-3 was dependent on patient’s weight (see Table 1).

**Table 1 T1:** Dosage of omega-3 fatty acids

**Body weight [kg]**	**Approx. total omega-3 daily dose [mg]**	**DHA daily dose [mg]**	**EPA daily dose [mg]**	**Dosage scheme**
**Under 40**	450	267	177,5	Twice a day
**40-60**	900	534	355	Twice a day
**Over 60**	1300	800	532,5	Twice a day

▪ Placebo/comparator group: the same dose of sunflower oil (containing omega-6 LC-PUFA).

Planned duration of the treatment is 24 weeks. Omega-3 and placebo are administered orally twice a day in the same dose and formulation of brown-colored and oval-shaped capsules. Capsules used in this study contain omega-3 LC-PUFA which was originally obtained from the marine algae. Study drugs were manufactured and blinded by Hasco-Lek, Poland® from the composition of the following ingredients: Incromega DHA 500 TG SR, Croda, Poland® (consisting of 100 mg/g EPA and 500 mg/g DHA) and Incromega EPA 500 TG SR, Croda, Poland® (consisting of 500 mg/g EPA and 100 mg/g DHA).

Throughout the whole treatment period (6 months) and next 6 months of the follow-up patients are advised to lose weight based on modification of their lifestyle (low-calorie diet and physical exercise). Pharmacological agents e.g. vitamin E, metformin, thiazolidinediones, statins, UDCA, probiotics or any that may affect body weight reduction, insulin resistance, lipid profile or fatty liver are not allowed to use during the trial.

### Dietary assessment

Simultaneously with pharmacological treatment, each patient received individually tailored dietary recommendations aimed to reduce body weight.

Detailed information about current quantity and quality of the patient’s diet was gathered by an experienced dietician in every center. Dieticians analyzed intake of total energy, essential nutrients as proteins, carbohydrates (including sucrose), fiber, lipids, main minerals, lipid- and water-soluble vitamins, cholesterol, saturated fatty acids, monounsaturated fatty acids and LC-PUFA including α-linoleic acid (ALA), linolenic acid (LA), arachidonic acid (ARA), DHA and EPA.

Various assessment methods including food records and dietary recalls are subjected to considerable error and bias, and none of these is considered as a 'gold standard' [25]. In our study dietary data were collected from patients and their parents using 3-days record (3dr) and food frequency questionnaire (FFQ). To assess portion size we used Album of Photographs of Food Products and Dishes by National Food and Nutrition Institute in both methods.

